### Study End Points and the Road Map for Their Evaluation

Students’ well-being will be assessed longitudinally by the 5-item World Health Organization Well-Being Index (WHO-5) at week 0, week 8, week 10, month 6, and month 12. The WHO-5 well-being index is a short global rating scale that measures subjective well-being for all populations, including adolescents. Positive well-being is another term for mental health (Figure 1) [33]. The key outcome measure includes the positive change in well-being, as estimated by the difference in postintervention (week 8 and week 10) and preintervention (week 0) WHO-5 mean scores by determining the *P* value and effect size using appropriate statistical tests. Although a difference in the mean WHO-5 score of >10 is considered clinically significant [33,34], a meta-analysis of meta-analyses concluded that universal prevention programs of this type in children have effect sizes between 0.07 and 0.16 [35]. Indeed, the difference in the mean WHO-5 score with an antidepressant (desvenlafaxine) vs placebo and wake therapy vs exercise was statistically significant but not clinically significant in patients with depression [36,37].

In children, the hope theory has been introduced on the concept that “goal-directed hopeful thinking” is a requisite for development and survival and is related to experiencing positive emotions [39-41]. Hope within students (≤16 years of age) will also be assessed longitudinally by age-appropriate hope scales at week 0, week 8, week 10, month 6, and month 12. Any improvement in “hope” will be estimated by the difference in postintervention (week 8 and week 10) and preintervention (week 0) mean scores by determining the *P* value and effect size using appropriate statistical tests. Hope theory is related to the theories of learned optimism, self-esteem, and self-efficacy, which are the key goals of the success4life program [42]. Students with “higher hope” have been found to attain higher academic achievement (at all levels of education) and higher graduation rates. They are also better problem-solvers and psychologically adjusted, can handle stress better, are healthier, and have higher self-esteem [43].

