### Ethics Considerations

At week 0, interested participants’ legal guardians will complete the “enrolment agreement form” as part of the onboarding process for parents and guardians. Informed consent will be obtained from the legal guardians of students. The program’s effectiveness will be assessed by a series of web-based questionnaires conducted on recruited students whose parents or guardians provided informed consent for the study. All the research questionnaires directed to the students are entirely anonymous, voluntary, and close-ended.

The research methodology is exempt from the requirement of ethics committee approval according to the Office for Human Research Protections, US Department of Health and Human Services, as the survey questionnaires will be completely deidentified [53,54]. Any suspected cases of justifiable concerns related to physical or mental health will be brought to the attention of relevant responsible party (eg, school counselors, parents, or legal guardians).

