Two serious concerns with RWD include reproducibility and replicability [62]. Ideally, a study testing an intervention should be reproducible through not only direct replication (adopting the same methodology) but also conceptual replication (adopting a different methodology) [63]. For a universal PPI to have a viable future and make a public impact, it needs to be scaled up and delivered by multiple trainers on multiple sites [18]. Our main research will check the effectiveness of the same intervention (success4life program) upon scaling through the *train the trainer* program for conceptual replication of the intervention. Minor amendments in the intervention to fix any inefficiencies or flaws, as evidenced by pilot testing, are permitted and will be documented.

Students are generally reluctant to answer IBL questions about their own experiences or opinions, not only owing to fears about revealing personal information to peers but also because they are often afraid that they may give “wrong” answers [64-66]. To overcome this hesitancy, all IBL journal completions for our intervention are real-time, digital, technology-based submissions through an LMS that protects the student’s anonymity and privacy to peers. A clear statement that there are no right or wrong answers will be implemented in all journals during each workshop. The PPIs designed to improve well-being are often compared to waitlist controls, which leaves ambiguity and unmeasured confounders related to their effectiveness [67]. Hence, we will not have any separate control group and will only study the change from baseline.

Randomized controlled trials (RCTs) with homogeneous study populations and double-blind study designs with statistical sample size and study calculations before the start of the study are the gold standard for determining the efficacy of interventions [68]. Our study lacks an RCT study design and a statistical sample size calculation, which could introduce bias. We decided to adopt an RWD design because RCTs on universal social and emotional learning programs have shown controversial findings [69], as often digital interventions show meaningful improvements only when tested under strictly controlled research settings [70]. Furthermore, although RCTs carry a high internal validity, the external validity or generalizability of the results to a wider population is always a concern with RCTs owing to strict inclusion and exclusion criteria [68,71].

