Nonetheless, real-world studies on heterogeneous populations without randomization are subject to bias and confounders [71]. The scientific best practices roadmap we adopted for scientific strategies needed to draw valid causal conclusions on the effectiveness of the success4life program includes the adoption of robust and validated study end points and publishing of the study protocol to enhance study transparency. We also use neutral instead of negatively or positively phrased items and measures to avoid central tendency bias (in Likert scales) for the weekly workshop feedback questionnaires, using closed questions in the survey. We decided to make the response to all questions mandatory for submission of each feedback questionnaire to avoid any issues of missing values in data sets and to keep the surveys fully anonymous yet voluntary to prevent nonresponse bias [59,63,72,73].

Pessimistic explanatory style (self-talk and the way people explain to themselves why they experience bad or good events) leads to cognitive vulnerability to depression, poor health, and early mortality [74,75]. Many factors—for example, the explanatory style of parents (especially that of mothers) for their and their children’s events along with childhood trauma, chronic adversity, and abuse—influence the development of a pessimistic explanatory style as a trait [74-76]. Interventions aimed at changing a pessimistic explanatory style and outlook enhance mental and physical well-being and lower the likelihood of future illnesses [76,77]. This is also relevant for breaking the cycles of intergenerational trauma and ever-increasing psychological distress in the youth by promoting protective processes that not only buffer against life’s uncertainties but also intergenerational risk and provide immunization against mental health disorders [78,79].

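### All surveys are declared entirely anonymous and no linking code is described, so the planned change from baseline has no valid standard error and no check on selective dropout

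*Protocol article*

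**What the plan says.** **Anonymity.** Under Ethics Considerations: "All the research questionnaires directed to the students are entirely anonymous, voluntary, and close-ended". The statement covers all research questionnaires, so it includes the WHO-5 and the hope scales. The same section rests the exemption from ethics committee approval on this property, "as the survey questionnaires will be completely deidentified". The Discussion repeats it as a deliberate choice, to "keep the surveys fully anonymous yet voluntary to prevent nonresponse bias", in a paragraph mainly about the weekly feedback forms.

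**Design.** Under Study End Points, the main outcome "will be assessed longitudinally by the 5-item World Health Organization Well-Being Index (WHO-5) at week 0"; the remaining four waves fall at weeks 8 and 10 and at months 6 and 12. Hope follows the same schedule. The key outcome is the difference between post-intervention (weeks 8 and 10) and week 0 mean scores, with a P value and an effect size from unnamed tests. The Discussion rules out a control group and "will only study the change from baseline".

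**Linkage.** The article mentions no study code, self-generated code or key that would join a student's answers from one wave to the next.

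**The concern.** With no comparator, each student's own baseline is the only reference for the key outcome. A longitudinal change-from-baseline design needs to know which week 0 answer belongs with which week 10 answer. The article fixes a property of the data (full anonymity) that, with no code described, removes that knowledge.

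Two things are at stake. First, the standard error of the change depends on the within-student correlation and on how many students answered both waves, and neither can be seen in unlinked data. Second, participation is voluntary, so the students who answer at week 10, month 6 or month 12 may differ from those who answered at week 0. Without a link, completers cannot be set against their own baseline. The mandatory-response rule in the Discussion closes gaps within a submitted form but does nothing about a missed wave.

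The same problem affects the week 8 to week 10 contrast, which is meant to show the effect of project-based learning. It also carries into phase 2, which uses phase 1 as its external control.

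**Working it through.** The plan has no figure to reproduce: the Discussion says there is no statistical sample size calculation, and no alpha, power, SD or correlation is given.

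**Inputs from the article:** about 100 students in phase 1 (Results); effect sizes of 0.07 to 0.16, cited from a meta-analysis of meta-analyses (Study End Points) and taken here as SD units.

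**Assumed:** two-sided 5% test, equal SD at both waves (set to 1), correlation r = 0.3, 0.5 or 0.7 between week 0 and a later wave, no clustering. Normal approximation throughout.

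**1. Standard error.** If n0 and n1 students answer two waves and m answer both, the variance of the difference in means is 1/n0 + 1/n1 − 2rm/(n0·n1). Without a link, m and r are both unknown. With the same n students at both waves it becomes 2(1−r)/n. An independent-samples analysis uses 2/n instead, so its SE is too large by 1/√(1−r).

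For n = 100 the independent-samples SE is √(2/100) = 0.1414. The true SE is √(1.4/100) = 0.1183, √(1.0/100) = 0.1000 or √(0.6/100) = 0.0775.

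**2. Size and power when the same 100 students answer both waves.**
- True size of the unpaired test: 2[1 − Φ(1.96/√(1−r))]
- Paired power at effect d: Φ(d/SE_true − 1.96)
- True power of the unpaired test: Φ((d − 1.96 × 0.1414)/SE_true)

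Example, r = 0.5, d = 0.16: paired Φ(1.60 − 1.96) = Φ(−0.36) = 0.36; unpaired Φ((0.16 − 0.277)/0.100) = Φ(−1.17) = 0.12.

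| r | SE too large by | true size of unpaired test | true power, unpaired, d = 0.16 | power, paired, d = 0.16 |
|---|---|---|---|---|
| 0.3 | 1.20 | 1.9% | 16% | 27% |
| 0.5 | 1.41 | 0.6% | 12% | 36% |
| 0.7 | 1.83 | 0.03% | 7% | 54% |

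**3. Selective dropout.** Let a fraction q leave, scoring g SD below those who stay, and let the stayers' mean not move. The week 0 mean over everyone lies q·g below the stayers' mean, and the later wave shows the stayers only, so the wave mean rises by q·g with no real change. For q = 0.20: 0.20 × 0.3 = 0.06 SD and 0.20 × 0.5 = 0.10 SD. For q = 0.10 the rise is 0.03 to 0.05 SD; for q = 0.30 it is 0.09 to 0.15 SD. The cited effects are 0.07 to 0.16. If the leavers scored higher than the stayers, the bias would run the other way.

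**The case against.** The strongest reply is that silence about a code does not prove there is none. The article also calls the data deidentified, deidentified data can carry a code, and a condensed article may leave such mechanics to the full protocol. This stands in part: a reader might infer that the responses can never be linked, and the text does not say so. But the article does more than stay silent. It asserts full anonymity for every questionnaire and builds its exemption on complete deidentification, so a code held elsewhere would still have to be squared with this wording.

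A reader might also infer that the planned change cannot be computed at all. The article does not support that. The key outcome is written as a difference in mean scores, which unlinked waves give directly, and with complete response it equals the mean within-student change. Nor does anonymity make the estimate itself noisier when the same students answer: its true sampling variance is 2(1−r)/n either way. What is lost is a valid estimate of that variance, and the error is conservative.

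A third tempting inference is a contradiction with the promise that "Any suspected cases of justifiable concerns related to physical or mental health will be brought to the attention of relevant responsible party". The article does not say that such concerns would come from survey answers. They could arise in the weekly live sessions or from journals that instructors mark in the learning management system, so no contradiction is shown.

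Finally, anonymity is offered as protection against nonresponse bias. It may well help participation, but without a link any nonresponse that does occur cannot be diagnosed.

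**Conclusion.** The concern holds in a limited form. As written, the anonymity statements and the longitudinal change-from-baseline design do not fit together, because no means of pairing the waves is described. The difference in wave means survives. A valid standard error and any check of completers against their own baseline do not.

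At r = 0.5 the unpaired analysis has about a third of the paired test's power at 0.16 SD (12% against 36%). Across r = 0.3 to 0.7 the figures are 16% to 7% against 27% to 54%. These rest on the assumed correlation, alpha, equal SDs and full overlap of responders. The 0.16 is the top of a cited range and not an effect the plan adopts. Even the paired test stays below 80% power there, so linkage does not by itself make phase 1 adequately powered.

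The dropout bias is the more troublesome part, because it can mimic benefit: 0.06 to 0.10 SD in the 20% example, with assumed dropout and score gap. Answers collected without a link cannot be joined afterwards, so this has to be settled before week 0.

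**What to change.** - Before week 0, add a self-generated, non-identifying code field to the WHO-5 and hope surveys, and have each student enter the same code at all five waves. The weekly feedback forms can stay as they are.
- State that the key outcome is analysed as within-student change from week 0, by a paired test or a mixed model over all waves, and compare the baseline scores of those who do and do not answer later.
- Reword the anonymity and exemption statements so that they describe coded responses that identify nobody.
- If no link is wanted, declare an unlinked repeated cross-sectional analysis and state its limits on precision and dropout.

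The cost is one field per survey and revised wording. Some codes will fail to match, students may feel slightly less anonymous, and the basis of the exemption has to be rechecked against the new wording.

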## Results

The study has 2 phases. A pilot phase (phase 1) will involve the recruitment of approximately 100 adolescent students between the ages of 13 and 19 years from the United States. Coaching will be preferably digitally and mainly conducted by the creators of the modules (2 physicians and a psychology educator with a doctorate). Phase 2 will involve training the trainers program. The “new coaches” could be teachers and peer mentors (with nonscientific backgrounds) or psychology, medical, or science graduates and postgraduate students who will contribute to making a larger social impact once the program is fit to scale. The target number of participants in phase 2 will be between 500 and 1000. Results from phase 1 will serve as an external control to test the effectiveness of the scalability platforms. The sample size predictions for phases 1 and 2 are based on a similar PPI, the Hummingbird Project from the United Kingdom, which led to improvements in adolescents’ well-being, also measured using the WHO-5 [18]. We anticipate to start student recruitment by 2022 through partnering with schools, family, and youth organizations and aim to obtain the results of phase 1 pilot testing by 2023.

Overall, we expect to see positive effects on students’ well-being and to enhance competency for essential life skills, including coping with adversities through learned optimism, decision-making, problem-solving, resisting peer and social media influences, and self-control through our success4life program.

## Discussion

The scientific breakthroughs through effective vaccinations and medications have helped prevent severe COVID-19 infection and deaths [55,56]; however, much of the work remains unfinished until we effectively tackle the rising mental disorders in the youth [57]. The challenge is to continue to direct innovation and science to effectively “flatten the curve” of increasingly alarming psychological distress in the youth, especially adolescents [15,58].

In this paper, we describe a holistic program developed by our team aimed to tackle the key challenges faced by adolescents in the modern age with technology-enhanced, real-time, hands-on experience on positive psychology. Our program uses IBL and PBL techniques to provide teenagers and emerging adults with methods for adaptive coping for relieving stress, self-compassion, goal attainment, learned optimism and resilience, and self-protection. In addition, we include modules on the awareness of the dangers of substance use and vigilance on social media. To our knowledge, this is the first time such a program has been developed, and we propose here a method to test its effectiveness and scalability.

Real-world data (RWD) consist of information collected during routine clinical, counseling, or coaching practice [59-61]. Real-world evidence (RWE) originates from studies based on valid RWD collected outside traditional controlled clinical trial programs. RWD, however, involves inherent biases and must be fit for the purpose of generating RWE. Challenges of RWD include data quality, reproducibility, replicability, and accuracy, which may affect validity [59].

The research methodology for the generation of RWD includes implementation science, qualitative research, translational research, participatory research, surveys, precision medicine, and mixed methods research [60]. Deidentified anonymous data enable researchers to study the effectiveness of mental health interventions, treatment, and services by observing outcomes recorded within routine sessions [61].

Two serious concerns with RWD include reproducibility and replicability [62]. Ideally, a study testing an intervention should be reproducible through not only direct replication (adopting the same methodology) but also conceptual replication (adopting a different methodology) [63]. For a universal PPI to have a viable future and make a public impact, it needs to be scaled up and delivered by multiple trainers on multiple sites [18]. Our main research will check the effectiveness of the same intervention (success4life program) upon scaling through the *train the trainer* program for conceptual replication of the intervention. Minor amendments in the intervention to fix any inefficiencies or flaws, as evidenced by pilot testing, are permitted and will be documented.

Students are generally reluctant to answer IBL questions about their own experiences or opinions, not only owing to fears about revealing personal information to peers but also because they are often afraid that they may give “wrong” answers [64-66]. To overcome this hesitancy, all IBL journal completions for our intervention are real-time, digital, technology-based submissions through an LMS that protects the student’s anonymity and privacy to peers. A clear statement that there are no right or wrong answers will be implemented in all journals during each workshop. The PPIs designed to improve well-being are often compared to waitlist controls, which leaves ambiguity and unmeasured confounders related to their effectiveness [67]. Hence, we will not have any separate control group and will only study the change from baseline.

Randomized controlled trials (RCTs) with homogeneous study populations and double-blind study designs with statistical sample size and study calculations before the start of the study are the gold standard for determining the efficacy of interventions [68]. Our study lacks an RCT study design and a statistical sample size calculation, which could introduce bias. We decided to adopt an RWD design because RCTs on universal social and emotional learning programs have shown controversial findings [69], as often digital interventions show meaningful improvements only when tested under strictly controlled research settings [70]. Furthermore, although RCTs carry a high internal validity, the external validity or generalizability of the results to a wider population is always a concern with RCTs owing to strict inclusion and exclusion criteria [68,71].

Nonetheless, real-world studies on heterogeneous populations without randomization are subject to bias and confounders [71]. The scientific best practices roadmap we adopted for scientific strategies needed to draw valid causal conclusions on the effectiveness of the success4life program includes the adoption of robust and validated study end points and publishing of the study protocol to enhance study transparency. We also use neutral instead of negatively or positively phrased items and measures to avoid central tendency bias (in Likert scales) for the weekly workshop feedback questionnaires, using closed questions in the survey. We decided to make the response to all questions mandatory for submission of each feedback questionnaire to avoid any issues of missing values in data sets and to keep the surveys fully anonymous yet voluntary to prevent nonresponse bias [59,63,72,73].

Pessimistic explanatory style (self-talk and the way people explain to themselves why they experience bad or good events) leads to cognitive vulnerability to depression, poor health, and early mortality [74,75]. Many factors—for example, the explanatory style of parents (especially that of mothers) for their and their children’s events along with childhood trauma, chronic adversity, and abuse—influence the development of a pessimistic explanatory style as a trait [74-76]. Interventions aimed at changing a pessimistic explanatory style and outlook enhance mental and physical well-being and lower the likelihood of future illnesses [76,77]. This is also relevant for breaking the cycles of intergenerational trauma and ever-increasing psychological distress in the youth by promoting protective processes that not only buffer against life’s uncertainties but also intergenerational risk and provide immunization against mental health disorders [78,79].

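### The protocol claims a route to valid causal conclusions on effectiveness, but its uncontrolled before-after design cannot separate programme effect from drift

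*Protocol article*

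**What the plan says.** All references are to the protocol article.

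- **Design (Discussion).** Comparisons of positive psychology interventions with waitlist controls are said to be a practice "which leaves ambiguity and unmeasured confounders related to their effectiveness". The next sentence draws the consequence: "Hence, we will not have any separate control group and will only study the change from baseline".
- **Key outcome (Study End Points and the Road Map for Their Evaluation).** "The key outcome measure includes the positive change in well-being, as estimated by the difference in postintervention" (weeks 8 and 10) and preintervention (week 0) WHO-5 mean scores, assessed by P value and effect size. Hope is handled in the same way.
- **Causal claim (Discussion).** The authors present a roadmap of "scientific strategies needed to draw valid causal conclusions on the effectiveness of the success4life program". It "includes the adoption of robust and validated study end points and publishing of the study protocol to enhance study transparency". Neutral items, closed questions, mandatory responses and anonymity follow as survey-quality measures.
- **Phase 2 comparator (Results).** "Results from phase 1 will serve as an external control to test the effectiveness of the scalability platforms".
- **Disclosure (Discussion).** The article says it lacks a randomised design and a sample size calculation, and that "real-world studies on heterogeneous populations without randomization are subject to bias and confounders".

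**The concern.** A causal conclusion needs some estimate of how the same students' scores would have moved without the course. The planned contrast has none. Change from week 0 to weeks 8 and 10 contains any programme effect plus time trend, position in the school year, maturation and the effect of answering the same questions repeatedly. Time trend is a practical worry here: the Introduction describes youth mental health worsening after the pandemic, and recruitment was planned from 2022.

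The reason given for having no control does not support the choice. If a waitlist comparison leaves unmeasured confounding, removing the comparator takes none of it away and adds the time effects that a concurrent group would have shared.

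At stake is the headline inference. A small P value for change from week 0 could be read, on the article's own terms, as showing that the programme works. A null result could equally hide a benefit offset by downward drift.

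**Working it through.** **Step 1. Does any listed strategy supply the missing comparison?**

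| Element | What it does | Separates programme from drift? |
|---|---|---|
| Validated end points | Measures well-being and hope soundly | No |
| Published protocol | Limits selective reporting | No |
| Neutral items; mandatory responses | Quality of the feedback questionnaires | No, and not their purpose |
| Closed questions; anonymous, voluntary surveys | Response quality, nonresponse | No |
| Phase 1 as external control | Compares creator-led with trainer-led delivery | No; phase 1 is treated too |

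**Step 2. How much drift would be declared significant?** The article gives no alpha, power or sample size calculation, so there is no stated figure to reproduce. The following is an illustration.

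Inputs from the article: n of about 100 (phase 1) and 500 to 1000 (phase 2); effect sizes of 0.07 to 0.16 cited from a meta-analysis of meta-analyses.

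Assumptions: two-sided 5% test, equal SDs at both times, no dropout, zero programme effect, and pre-post correlation r = 0.6 (range 0.5 to 0.7).

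In linked pairs, the SD of change is √(2(1−r)) baseline SDs. At r = 0.6 this is √0.8 = 0.894. The smallest significant mean change is 1.96 × √(2(1−r)) / √n. If responses cannot be linked, it is 1.96 × √(2/n).

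| n | Linked, r = 0.6 | Linked, r = 0.7 to 0.5 | Unlinked |
|---|---|---|---|
| 100 | 1.96 × 0.894 / 10 = 0.175 SD | 0.152 to 0.196 | 0.277 |
| 500 | 1.96 × 0.894 / 22.36 = 0.078 SD | 0.068 to 0.088 | 0.124 |
| 1000 | 1.96 × 0.894 / 31.62 = 0.055 SD | 0.048 to 0.062 | 0.088 |

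These are critical values for the observed change. A true drift of exactly that size would be declared significant about half the time.

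**Step 3. How often would drift of the cited size be significant?** With linked pairs, the noncentrality is d√n / √(2(1−r)). The probability of P < 0.05 for drift d and no programme effect, with r = 0.5 to 0.7, is:

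| n | d = 0.07 | d = 0.16 |
|---|---|---|
| 100 | 11% to 15% | 36% to 54% |
| 500 | 35% to 52% | 95% to >99% |
| 1000 | 60% to 82% | >99% |

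The nominal rate is 5%. A larger sample makes misattribution more likely, because it sharpens the estimate of programme plus drift without dividing the two.

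**The case against.** The strongest reply is that the authors know the limits of the design and say so. They call randomised trials the gold standard, admit that lacking one could introduce bias, and warn that real-world data carry inherent biases. They also give a second reason for the design, namely generalisability. The first phase is a pilot, and the abstract's conclusion says only that they anticipate the programme can support improvement.

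This stands as far as it goes. An uncontrolled real-world study is a legitimate choice, and generalisability is a fair reason to prefer one. But the disclosure is general, names neither drift nor time trend, and is followed directly by the sentence claiming a causal route. It does not cure that sentence.

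Some stronger readings are tempting and go too far:

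- A reader might infer that drift will be reported as effectiveness. The document does not establish this: drift may be nil, or downward and mask a benefit.
- A reader might put regression to the mean first. The programme is universal and no low-score entry criterion is stated, so this depends on whether volunteers enrol at a low point, on which the article gives no information.
- A reader might take 0.07 to 0.16 as the plan's expected effect. It is cited as context for similar programmes. The article ties its sample sizes to a different project and adopts no target effect.
- The neutral wording and mandatory items should not be faulted for failing to handle drift; they are described for the feedback questionnaires.

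**Conclusion.** The causal claim is wrong as written. The design supports an estimate of uncontrolled change from week 0. The phase 1 comparison can at most contrast two ways of delivering the programme, and says nothing about the programme against no programme.

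On size, the phase 2 thresholds (0.055 to 0.078 SD if linked at r = 0.6; 0.088 to 0.124 SD if unlinked) fall within or below the cited 0.07 to 0.16 range, so drift no larger than the effects reported for such programmes could be significant by itself. Phase 1 is less exposed: at r = 0.6 its threshold of 0.175 SD lies just above that range, and at 0.277 SD if unlinked it lies well above. The figures depend on the assumed alpha, correlation, linkage and absence of dropout. The main conclusion does not, because no sample size separates drift from effect in this contrast.

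**What to change.** 1. Replace the causal sentence in the Discussion with a statement such as: *Phases 1 and 2 estimate uncontrolled change from week 0; no causal conclusion on the effectiveness of the programme will be drawn.*
2. Reword to match: the Objective and Conclusions in the Abstract, the aim at the end of the Introduction, and the effectiveness statements in Ethics Considerations and the Discussion. Describe the phase 1 versus phase 2 comparison as one of delivery modes.
3. Delete the argument that moves from the ambiguity of waitlist comparisons to having no control. The generalisability rationale can stay.

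The cost is wording only, and a less favourable claim.

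Optional, and only if a causal claim is wanted:

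- An extra pre-course survey would indicate drift before the programme starts. Enrolment and consent now take place at week 0 and would have to move earlier. Within-student comparison would need an anonymous linking code, since the questionnaires are fully anonymous. Without one, group means at successive times could still be compared.
- A concurrent comparator in phase 2 would address drift directly. This is a real redesign, of a kind the authors have declined, and is not needed if the claim is reworded.
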